#### Qualitative

##### Parents and children

To further investigate the feasibility and acceptability of FAME, semi-structured interviews with parents are held at *t*_1_ and *t*_3_. During *t*_1_, we aim to assess (1) whether participants feel that distressing experiences before, during, and after the flight have impacted their parenting skills and the parent-child relationship, (2) social support, (3) how participants cope with stressors, and (4) expectations concerning FAME. During *t*_3_, we aim to (1) study participants’ evaluations of the programme in terms of usefulness; (2) evaluate programme outcomes: social support, coping strategies, and the parent-child relationship; and (3) evaluate participant responsiveness. Open-ended questions will be posed to the family members. Subsequently, family members score their answers on a 5-point Likert scale. For example, the open-ended question “Which component of the programme was most helpful to you, and why?”, is followed by scoring the question “How helpful was this component?” on a 5-point Likert scale (1 *not helpful* to 5 *very helpful*). The topic list is based on brainstorm sessions with researchers and developers of the FAME programme.

### Statistical analysis

#### Analysis of quantitative data

Quantitative data-analysis will be conducted using SPSS 23 (IBM Statistics). Descriptive statistics of demographic data, the programme integrity list, and the rating scales will be presented for all participants. For continuous variables, means, standard deviations, medians, and ranges will be reported. For categorical variables, numbers and percentages will be reported.

To test the hypothesis that families living at family facilities have more problems concerning the parent-child relationship and family functioning and higher parental symptoms of anxiety and depression than families living at asylum centres, pre-test scores on the EAS, PHQ-4, and SCORE-15 will be compared between these two groups using independent *t* tests.

To evaluate whether undergoing FAME coincides with a reduction in parental symptoms of anxiety and depression and improvement in family functioning, differences between the pre- and post-test scores on the SCORE-15 and PHQ-4 will be calculated. If more than 40 participants have completed the pre- and post-test measures, a mixed-design ANOVA will be executed. However, if there is a large amount of missing data, or if less than 40 participants have completed pre-test and post-test measures, two independent *t* tests will be executed. In addition to statistical significance, it is important to report any meaningful clinical change when studying the impact of an intervention. Calculating the Reliable Change Index (RCI), as proposed by Jacobson and Truax [31], allows us to do so. Using the RCI, we will calculate whether the differences in the scores between *t*_1_ and *t*_3_ are greater than the measurement error. A calculated RCI larger than |1.96| indicates a clinically reliable change with 95% certainty. The RCIs allows us to determine the numbers of participants improved, unchanged, and worsened from *t*_1_ to *t*_3_.

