### Participants

Study participants will be recruited from the asylum-seeker family population in the Netherlands. Families will be selected through convenience sampling. Eligible families must meet the following criteria: (1) at least one caregiver participates in FAME, (2) at least one child aged 0–18 participates, and (3) the family lives in an asylum centre or family facility. Participants who are not able to function in a group, as reported by health teams of the family facility or asylum centre, are not eligible for this study. For example, participants who are likely to experience difficulties communicating in a group setting as a result of severe psychiatric illness, such as psychosis, will be excluded. Families with psychiatric problems, such as posttraumatic stress disorder or depression, who are likely to be able to benefit from FAME are included in the study. This will be discussed with the health teams prior to inviting the families to take part in the information session about FAME. Each group will include approximately five to eight families. Families will be divided over the groups based on the age of their child (0–5, 6–12, 13–18). However, this division cannot be followed strictly, for example, because some families have children in more than one age category. Therefore, the division will be used merely as a guideline. If there are multiple children in a family, parents are asked with which child they experience most difficulties and will be allocated to the age group of that child. All children of the family are invited to take part in the programme.

As this is a pilot implementation and evaluation of a programme that has not been studied previously, it was not considered appropriate to conduct a reliable sample size calculation. We aim to include approximately five living locations. In each location, we will recruit two groups of approximately six families. This will result in a total sample size of approximately 60 families (5 × 2 × 6). One or two parents and approximately one to two children of each family will take part, resulting in a total number of approximately 90 parents and 90 children.

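### Facility type is compared at baseline with independent t tests although it varies only between about five locations, so the false-positive rate is inflated by an amount that depends on an unstated intraclass correlation

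*Protocol article*

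**What the plan says.** Objective 4 (Objectives) concerns baseline differences and similarities between families in asylum centres and families in family facilities. The analysis section turns this into a directional test: "To test the hypothesis that families living at family facilities have more problems concerning the parent-child relationship and family functioning", with parental symptoms added. The method is fixed: "pre-test scores on the EAS, PHQ-4, and SCORE-15 will be compared between these two groups using independent *t* tests". No term for location or family is mentioned.

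Under Participants, the sampling runs by location: "We aim to include approximately five living locations. In each location, we will recruit two groups of approximately six families". One eligibility criterion is that "the family lives in an asylum centre or family facility", and Table 1 describes the two as separate placements in the asylum procedure. One or two parents per family take part, "resulting in a total number of approximately 90 parents and 90 children".

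The article does not give an ICC, a significance level for these tests, the number of locations of each type, or whether the unit of analysis is the parent or the family.

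**The concern.** On the article's description, everyone recruited at one location has the same facility type. The comparison is therefore between a few locations, for example three against two. Adding families at the same sites does not add units to that contrast.

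An independent t test on 90 parents works with 88 df and takes its standard error from the spread between individuals. Two sources of correlation are left out:

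- **Location.** Families are a convenience sample, and local health teams judge who can function in a group and help to invite them. Sites can differ for reasons unrelated to facility type.
- **Family.** Two parents in one family rate the same family on the SCORE-15 and share their circumstances when they complete the PHQ-4.

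One unusual site could then produce a significant result that is reported as a facility-type difference.

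**Working it through.** **The plan's own figures.** 5 × 2 × 6 = 60 families, and 60 × 1.5 = 90 parents. Both reproduce. Per location this is 12 families and 18 parents.

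**Assumptions, since the article is silent.** Two-sided 5% level; locations split 3:2; location ICC ρL from 0 to 0.10; additional family share of variance ρF from 0 to 0.5; families alternating one and two parents.

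**Step 1: variance inflation.** Total variance is set to 1. With six one-parent and six two-parent families, the sum of squared family sizes per location is 6 × 1 + 6 × 4 = 30. The variance of a location mean is

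v = ρL + ρF × 30/18² + (1 − ρL − ρF)/18.

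The t test in effect assumes 1/18. The ratio is 18v = 1 + 17ρL + 0.667ρF. With one score per family it is 1 + 11ρL.

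**Step 2: approximate actual error**, 2 × [1 − Φ(1.96/√ratio)].

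- Parent scores, ρL = 0.05, ρF = 0.3: ratio 1 + 0.85 + 0.20 = 2.05; 1.96/1.432 = 1.37; error about 17%.
- One score per family, ρL = 0.05: ratio 1.55; 1.96/1.245 = 1.57; error 11.5%.
- One score per family, ρL = 0.10: ratio 2.10; 1.96/1.449 = 1.35; error 17.6%.

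**Step 3: simulation** of the planned t test with no true difference, 20,000 runs per setting, 3:2 split:

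| Location ICC | 90 parents, ρF = 0 | ρF = 0.3 | ρF = 0.5 | 60 families, one score each |
|---|---|---|---|---|
| 0 | 5.0% | 7.4% | 9.2% | 5.1% |
| 0.01 | 6.8% | 9.3% | 11.0% | 6.2% |
| 0.02 | 9.0% | 11.4% | 12.9% | 7.9% |
| 0.05 | 14.9% | 17.4% | 18.8% | 11.8% |
| 0.10 | 23.9% | 25.8% | 26.7% | 18.5% |

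A 4:1 split gives nearly the same figures. These are rates per score. The test is applied to at least eight scores: six EAS components, the PHQ-4 and the SCORE-15.

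**Step 4: the alternative.** A t test on the five location means (3 df, critical value 3.18) kept its error between 4.6% and 5.2% in every setting.

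Its precision is poor. For a 3:2 split, SE = √[v(1/3 + 1/2)]. At ρL = 0.05 and ρF = 0.3, v = 0.050 + 0.028 + 0.036 = 0.114, SE = 0.308, and the 95% half-width is 3.18 × 0.308 = 0.98 SD. Power for a 0.5 SD difference, from the noncentral t, with ρF of 0 to 0.3:

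- ρL = 0.01: 29–32%
- ρL = 0.05: 21–23%
- ρL = 0.10: 16–17%

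Averaging parents within family first gives v = ρL + ρF/12 + (1 − ρL − ρF) × 0.75/12, because the mean of 1/(parents per family) is 0.75. At ρL = 0.05 and ρF = 0.3 this is 0.116, so the result hardly changes.

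**The case against.** The strongest reply is that the inflation may be small. No ICC is given, the unit of analysis is not stated, and the hypothesis is worded about families. With one score per family and a location ICC of 0.01 to 0.02, the error is only about 6–8%. This stands. A reader might infer that the false-positive rate is several times 5%, but the document does not support that as a fact. The error reaches about three times nominal only from a location ICC of about 0.05 with parent scores, or somewhat above that (18.5% at 0.10) with one score per family. Parent level is the natural reading for the PHQ-4 and SCORE-15, which parents complete themselves, but it remains an inference.

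The 90-parent figures also should not be carried over to the EAS. It is scored on videotaped parent–child pairs whose families agree to filming, and the number of pairs is not stated.

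A reader might add that the confidence intervals will be too narrow. The analysis section plans none for this comparison, so that charge has no basis.

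The Discussion already urges caution because of small sample size and convenience sampling, and this is the fourth objective of a pilot. No later decision in the article is tied to it. That lowers the weight of the point. It does not answer it: clustering is not mentioned, a general caution does not correct a standard error, and the comparison is still worded as a hypothesis test.

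**Conclusion.** The point holds. A contrast between about five locations is to be tested as if parents or families were independent, and the test cannot separate facility type from site. Any positive location correlation raises the error above nominal. With parent-level scores, family correlation alone does so as well (7.4% at ρF = 0.3 with no location effect).

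The direction is certain and the size is not. Over location ICCs of 0 to 0.10 the error runs from about 5% to 27% with parent scores, and from about 5% to 18% with one score per family. These figures rest on the assumed 5% level, the ICC range, equal location sizes and a single facility type per location. Severity is moderate. The feasibility and acceptability objectives are not affected.

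**What to change.** In Analysis of quantitative data, replace the independent t tests for objective 4 with:

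1. Scores averaged within family, then the mean for each location, shown location by location.
2. An estimated facility-type difference between location means, with an interval on locations minus 2 df.
3. A statement that the comparison is exploratory and not a hypothesis test, and that with so few locations it cannot separate facility type from site.

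This changes wording and analysis only, and needs no new data. Recruitment began in September 2018 (Trial status), so the fix does not depend on how the locations are split. If only one location of a type is recruited, its interval rests entirely on the spread among the others, and the report should say so.

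The cost is a wide interval (roughly ±1 SD at a location ICC of 0.05) and low power, about 16–32% for a 0.5 SD difference at location ICC 0.01 to 0.10. That reflects what about five locations can show.

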As noted, FAME involves seven weekly 2–3-h sessions. One or two official interpreters will be provided in each group. At the end of each session, the participants are asked to fill in scales measuring their distress and how they rate the session (*t*_2_). The scales will be explained by the trainer, who is aided by the interpreters. Moreover, during the sessions, a researcher will evaluate programme integrity using a predetermined programme integrity list (see below). The final assessment (*t*_3_) takes place in the week after the last session of FAME. The participants will be visited at home or a private room will be arranged. A (telephone) interpreter will be provided. The parents and children aged five and over will take part in individual semi-structured interviews. Parents will fill in questionnaires. Post-test measures will last approximately 65 min for the parents and 30 min for the children. See Table 3 for the schedule of enrolment, intervention, and assessment.

**Table 3 Tab3:** Schedule of enrolment, intervention, and assessment

		Parents			Children		
Time point	Enrolment	*t* _1_	*t* _2_	*t* _3_	*t* _1_	*t* _2_	*t* _3_
Enrolment							
Eligibility screen	X						
Informed consent	X						
Information session	X						
Assessments							
SCORE-15		X		X			
PHQ-4		X		X			
Semi-structured interview		X		X			X
Demographics		X					
EAS		X			X		
((Y)C)ORS			X			X	
((Y)C)SRS			X			X	
Programme integrity list			X			X	

*t*_1_, pre-FAME; *t*_2_, weekly assessments during FAME; *t*_3_, post-FAME. *EAS* Emotional Availability Scales, *PHQ-4* Patient Health Questionnaire for Depression and Anxiety, *SCORE-15* Systematic Clinical Outcome and Routine Evaluation, *((Y)C)ORS* ((Young) Child) Outcome Rating Scale, *((Y)C)SRS* ((Young) Child) Session Rating Scale

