When executing the proposed study, several barriers can be anticipated. For example, when working with asylum-seeker families, we have to keep into account the many relocations the families are faced with. Families living in asylum centres are often placed in another centre or move away from the centre after the asylum has been granted. Families living at family locations risk deportation. These replacements can result in heightened levels of dropout. Moreover, asylum-seekers are faced with post-migration stressors concerning acculturation and resettlement, such as financial issues, language barriers, and facing an insecure future. These continuous stressors might make it difficult to prioritize preventive programmes such as FAME [3, 9]. To deal with these issues concerning recruitment and inclusion, trainers will collaborate with local health teams in order to reach families, inform them about FAME, and remind them of the sessions as best as possible. To further inform families, the initial information session will focus on disclosing the aim of FAME and the study and clarify mutual expectations. Finally, in order to overcome barriers, FAME is offered at the living locations of the families, diminishing travelling costs and time spent travelling. Nevertheless, the current study will not be able to eliminate dropout as a result of factors such as relocation. These barriers underline the need for studying the feasibility of FAME.

The current study holds several limitations. Because of the small sample size and convenience sampling, the results and their generalizability should be interpreted with caution. Moreover, concerning our objective to establish the potential effectiveness of FAME, we will be unable to attribute any potential effects to FAME as a result of the lack of a control group. However, in line with the developmental cycle proposed by Weine [19], the scope of the current study is not to provide such an extensive evaluation, but to take a next step in the development of a recently developed programme. Possibly, the study will allow us to determine important parameters to estimate the sample size and detectable effect sizes for potential future, larger studies assessing the effectiveness and implementation of FAME.

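### The pre-post test for PHQ-4 and SCORE-15 is chosen after the data are seen, by a completer rule with an undefined trigger, and the fallback test does not suit paired, incomplete data

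*Protocol article*

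**What the plan says.** All of the analysis rule stands in the protocol article under Analysis of quantitative data.

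- **Quantity analysed:** "differences between the pre- and post-test scores on the SCORE-15 and PHQ-4 will be calculated". Table 3 schedules both instruments for parents only, at t1 and t3.
- **Main method:** "If more than 40 participants have completed the pre- and post-test measures, a mixed-design ANOVA will be executed".
- **Fallback:** the next sentence, introduced as an exception, substitutes two independent-samples t tests "if there is a large amount of missing data, or if less than 40 participants have completed pre-test and post-test measures". It does not say which two sets of scores are compared.
- **Individual change:** the Reliable Change Index is used to "determine the numbers of participants improved, unchanged, and worsened from" t1 to t3. No category is given for parents without t3.

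The Participants section plans about 60 families and about 90 parents. The Discussion names transfer to another centre, moving out once asylum is granted, and deportation, and adds: "These replacements can result in heightened levels of dropout". It gives no rate and accepts that such dropout cannot be eliminated. For t3, the Procedure section says: "The participants will be visited at home or a private room will be arranged". It also provides a (telephone) interpreter.

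**The concern.** A prespecified analysis should tell the analyst what to do for any data set that arrives. This rule does not. One trigger is a count and another is an undefined quantity of missing data, and both can hold together. Whoever applies the rule must decide, with the data in hand, whether the loss is large enough to change the test. That leaves room to choose a method by its result.

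The direction of the switch is also unhelpful. More missing data leads to a simpler test that does not deal with missing data and may throw away the within-parent pairing.

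The main path uses only parents with both scores. Some of the reasons the article gives for leaving, a granted application or deportation, could plausibly affect distress and family functioning, and they differ between the two types of housing. At stake are the preliminary estimate of change and the reliable-change counts. The Discussion hopes that parameters from this study will help to size larger ones, so a distorted estimate could carry forward.

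**Working it through.** **1. Planned numbers (Participants section).** Families: 5 × 2 × 6 = 60, as stated. Parents: one or two per family gives 60 to 120; at 1.5 per family, 60 × 1.5 = 90, as stated. No power calculation is given, so there is none to reproduce.

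**2. What the count threshold means.** Share missing = 1 − completers / parents enrolled.

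| Parents enrolled | Missing at 41 completers | Missing at exactly 40 |
|---|---|---|
| 60 | 1 − 41/60 = 31.7% | 33.3% |
| 90 | 1 − 41/90 = 54.4% | 55.6% |
| 120 | 1 − 41/120 = 65.8% | 66.7% |

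With 90 parents, losses of 20%, 40% and 50% leave 72, 54 and 45 completers. All meet the ANOVA count. Whether the override applies at any of them depends on what counts as large. At exactly 40, neither more than 40 nor fewer than 40 is true, so no method follows from the count.

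**3. What the fallback can be testing.** Two readings are open.

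- *All t1 scores against all t3 scores.* Parents with t1 only can enter, but the pairing is ignored. With equal variances and correlation ρ between t1 and t3, the standard error relative to a paired test is 1/√(1 − ρ): 1.20, 1.41 and 1.83 for assumed ρ of 0.3, 0.5 and 0.7. Normal-approximation power at n = 39 pairs and an assumed change of 0.4 SD is Φ(0.4/√(2/39) − 1.96) = 42% unpaired. Paired, it is Φ(0.4/√(2(1 − ρ)/39) − 1.96) = 56%, 70% and 90% for the same ρ.
- *One housing group against the other.* This does not test whether scores change from t1 to t3, which is the objective.

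**4. Who is in the main result.** A change score needs t1 and t3. A two-time-point mixed-design ANOVA in its standard form deletes cases lacking either. The Reliable Change Index needs both. No stated step brings parents without t3 into any of the three.

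**5. How far completers could differ from the enrolled cohort.** Completer mean change − cohort mean change = share lost × (mean change in stayers − mean change in leavers). The article gives neither input. For an assumed absolute difference of 0.2 to 0.5 SD:

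- 20% lost: 0.04 to 0.10 SD
- 40% lost: 0.08 to 0.20 SD
- 54% lost: 0.11 to 0.27 SD

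The sign may go either way.

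**The case against.** The strongest reply is that the two sentences do not contradict each other. The second is worded as an exception, so the ordinary reading is ANOVA above 40 unless missing data are large. That stands. A reader might infer that the rule orders two tests at once, but the text supports only an override with no threshold and a gap at exactly 40.

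Other parts of the reply also stand:

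- A reader might infer that every parent without t3 is dropped whichever branch is used. The fallback is too vague to show this; it could include t1-only parents, unpaired.
- A reader might infer that leavers' data are thrown away. They are not: baseline PHQ-4, SCORE-15 and EAS scores enter the housing comparison, and the rating scales are described for all participants. Leavers are lost only to the pre-post result.
- Transfer to another centre is among the stated reasons for leaving and need not relate to the outcomes. The article expects heightened dropout but gives no rate, so calling it heavy goes beyond the text.
- A mixed model does not correct for loss that depends on unseen t3 scores.
- This is an uncontrolled pilot that disclaims attribution, and missing-data detail may sit in a fuller document.

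The last point does not dispose of the concern. The article does not leave the method open; it fixes a rule, and a later plan would have to override that rule.

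**Conclusion.** The concern holds in this form: the choice of pre-post test depends on the data through an undefined trigger, leaves exactly 40 completers unassigned, and falls back on a test that does not address missing data and either ignores pairing or misses the question. This follows from the text and the planned 90 parents alone.

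That the main result may describe mainly families who stayed follows from the stated methods and the stated reasons for leaving. How much this matters cannot be determined from the article. The 0.04 to 0.27 SD range rests on assumed losses and differences. A reader might infer that the benefit will be overstated, but families who leave with asylum granted could improve more than those who stay, so understatement is equally possible. The power figures likewise rest on assumed correlations and an assumed change.

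The consequence is an avoidably imprecise and possibly unrepresentative preliminary estimate, not a wrong confirmatory conclusion. It should be corrected because correction costs little.

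**What to change.** Delete both triggers, the count of 40 and "if there is a large amount of missing data", together with the fallback t tests. Prespecify, for PHQ-4 and SCORE-15 separately, one likelihood-based linear mixed model on all observed t1 and t3 scores at any sample size, with time, facility type and their interaction. It keeps the pairing and uses parents with only one score.

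Alongside it:

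- compare baseline scores of completers and leavers;
- report the counts improved, unchanged and worsened together with the number lacking t3;
- state that the model corrects only for dropout explained by observed data.

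These are changes of wording and need no new data.

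Optionally, allow t3 PHQ-4 and SCORE-15 by telephone when a family has moved, using the interpreter service already foreseen, and record the mode and the reason for leaving. The cost is tracing effort, a possible mode effect and incomplete reach, since some families will not be found.

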### Objectives

The current pilot study aims to evaluate the feasibility, acceptability, and potential effectiveness of FAME to reduce parental mental health problems and improve family functioning. As families living in family locations might suffer from increased levels of distress, we expect these families to have more difficulties concerning the parent-child relationship, parental symptoms, and family functioning than families living in asylum centres. Therefore, baseline distress levels of both categories of families will be compared. Specifically, the objectives are to determine:Whether it is feasible to offer FAME to families living in Dutch asylum centres and family facilities.Whether FAME is acceptable to asylum-seeker families.Whether undergoing FAME coincides with a reduction in parental symptoms of anxiety and depression and improvement in family functioning.Baseline differences and similarities in the parent-child relationship, parental symptoms of anxiety and depression, and family functioning between families living in asylum centres and families living in family facilities.

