## Methods/design

### Trial design

An uncontrolled, two-group pre-test-post-test design will be conducted, using a mixed-methods approach. Standardized questionnaires, semi-structured interviews, an observational scale, and a (self-constructed) programme integrity list will be used. The programme, including measurements, will take approximately 10 weeks per group.

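### Objective 3 asks for the overall change from t1 to t3, but neither planned test is a direct paired estimate of it

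*Protocol article*

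**What the plan says.** The third objective is to determine "Whether undergoing FAME coincides with a reduction in parental symptoms of anxiety and depression and improvement in family functioning". The comparison between asylum centres and family facilities is a separate, fourth objective, and it concerns baseline only: "Therefore, baseline distress levels of both categories of families will be compared". It has its own t tests on the pre-test scores.

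The Trial design section says: "An uncontrolled, two-group pre-test-post-test design will be conducted, using a mixed-methods approach". All families are offered the programme. The two groups that the analysis section compares are the residents of family facilities and of asylum centres.

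For the third objective, the section Analysis of quantitative data begins with "differences between the pre- and post-test scores on the SCORE-15 and PHQ-4 will be calculated". It then makes the test depend on the number of completers: "If more than 40 participants have completed the pre- and post-test measures, a mixed-design ANOVA will be executed". The alternative, a pair of independent t tests, applies "if there is a large amount of missing data, or if less than 40 participants have completed pre-test and post-test measures". Reliable Change Indices are added, to count participants as improved, unchanged or worsened.

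On software: "Quantitative data-analysis will be conducted using SPSS 23 (IBM Statistics"). On recruitment: "We aim to include approximately five living locations", with two groups of about six families in each, giving about 60 families and 90 parents.

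**The concern.** The third objective concerns one quantity per outcome: the average change of the parents who took part. The direct analysis is the mean of the paired differences with its confidence interval. The plan departs from this in both branches.

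- Above 40 completers, a mixed-design ANOVA brings in a between-subject factor for which the objective has no use. Its time effect need not be the mean change of the parents, and its group-by-time effect answers no stated objective.
- Otherwise, independent t tests do not use the fact that the same parents are measured twice.

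The estimated change could therefore differ from the average change of the families treated, could be less precise than it need be, and would change its nature with the number of completers. This matters even in a pilot, because the Discussion hopes that the study will supply parameters for sizing later trials.

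**Working it through.** **Inputs from the article.** 5 locations × 2 groups × 6 families = 60 families. With one or two parents per family, taken as 1.5, 60 × 1.5 = 90 parents. Both stated totals are reproduced. The article does not give the split of locations or parents by type, the between-subject factor, the type of sums of squares, or the SD of the change.

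**Assumptions.** The factor is living condition, the model includes its interaction with time, and sums of squares are Type III (taken as the default of the named software). The SD of the change is 1 in both types, parents are independent, and alpha is 0.05 two-sided. The splits 3:2 and 4:1 illustrate how five locations could divide.

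**Step 1: what each analysis estimates.** Let the mean changes be dA and dB in groups of size nA and nB, with N = nA + nB.

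- Time effect under these assumptions: (dA + dB)/2.
- Mean paired difference: (nA·dA + nB·dB)/N.

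In a simulated data set with 33 and 8 parents, the time effect was −0.506, the unweighted mean of the two changes, against a pooled change of −0.222 (p = 0.011 against 0.170 for the paired test). Change-score and long-form models gave the same F, 7.125. Without the interaction term the time coefficient was −0.222, so the equal weighting depends on the model.

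**Step 2: precision.** The variance of the time effect relative to that of the paired mean is 0.25 × (1/nA + 1/nB) × N.

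| Split | nA : nB | Smaller type's share | Its weight in the time effect | Variance ratio |
|---|---|---|---|---|
| 3:2 of 90 | 54 : 36 | 40% | 50% | 0.25 × (1/54 + 1/36) × 90 = 1.04 |
| 4:1 of 90 | 72 : 18 | 20% | 50% | 0.25 × (1/72 + 1/18) × 90 = 1.56 |
| about 4:1 of 41 | 33 : 8 | 20% | 50% | 0.25 × (1/33 + 1/8) × 41 = 1.59 |

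At 72:18, the 90 parents carry the information of 90/1.56 ≈ 58.

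**Step 3: shift of the estimate.** Suppose the change is 0.2 SD in the larger type and 0.6 SD in the smaller. The time effect is (0.2 + 0.6)/2 = 0.40 at any split. The paired mean is (54 × 0.2 + 36 × 0.6)/90 = 0.36 at 3:2 and (72 × 0.2 + 18 × 0.6)/90 = 0.28 at 4:1. With equal changes or equal group sizes the two estimates coincide.

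**Step 4: effect on the test.** Probability of a significant result, time effect against paired test, from 20,000 simulations per case:

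| True change (larger; smaller type) | 33 : 8 | 72 : 18 | 54 : 36 |
|---|---|---|---|
| 0; −0.8 SD | 50% v 14% | 85% v 28% | 96% v 82% |
| −0.5 SD; 0 | 23% v 69% | 47% v 96% | 64% v 79% |
| −0.4 SD; −0.4 SD | 50% v 70% | 85% v 96% | 96% v 96% |
| 0; 0 | about 5% both | about 5% both | about 5% both |

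**Step 5: the other branch.** With n parents, score variance s² at both times and correlation r between t1 and t3, the variance of the mean difference is 2s²(1 − r)/n. An independent t test of t1 against t3 uses 2s²/n, which is too large whenever r is positive. The article gives no r, so no size is put on this. If the independent t tests were instead meant to compare the two location types, they would not address overall change at all.

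**The case against.** The article is condensed, and the factor, the effect of interest and the type of sums of squares may stand in a fuller plan. Age group is another conceivable factor, although it has three bands and is used only as a rough guide, so it fits a two-group label less well. An equal-weight average over two living conditions is a legitimate quantity if chosen on purpose, and its test keeps the 5% level when neither type changes. Having location in the model is defensible where the two settings are expected to differ in distress. The plan also calculates the pre-post differences and the Reliable Change Indices, in which each participant counts once. The word independent in the fallback may be a slip for paired.

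Most of this stands, and it makes the weighting problem conditional. It does not remove the mismatch between the question and both named tests, which is in the text itself. No intention to weight the settings equally is stated, and counts of reliable change do not give a mean change with an interval.

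A reader might go further and infer that one small group will supply half of the main result, or that facility families will be lost more often. The documents do not support either. Half the weight is not half the result, since that depends on the changes observed. No primary outcome is declared, and feasibility and acceptability are objectives in their own right. The Discussion gives a reason for dropout in each setting without saying which will lose more. The split between settings is not stated.

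**Conclusion.** The point holds in a limited form. For the third objective, neither branch is a direct paired estimate of overall change; this follows from the text alone. That the ANOVA time effect weights the location types equally is a likely inference, conditional on the living-condition factor, its interaction and Type III sums of squares. Under that reading the loss is small at 3:2 and material only near 4:1, and it shifts the estimate only if the two types change by different amounts. The figures ignore clustering by family, group and location. Because the size is uncertain and the remedy nearly free, the change should be made, but the plan is not shown to give a seriously wrong answer.

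**What to change.** For the third objective, define the estimate for each of PHQ-4 and SCORE-15 as the mean of the individual t3 minus t1 differences over all parents with both measures, with a 95% confidence interval. Use it whatever the number of completers, in place of both the ANOVA time effect and the independent t tests. Show the mean change in each living condition beside it, and label any group-by-time test exploratory and not part of the answer to this objective.

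The cost is a change of wording, with no new data: one overall and two group-specific estimates per outcome replace the ANOVA table, and this estimate no longer depends on the 40-completer threshold. The downside is that the pooled estimate reflects the mix of location types in the sample; the group-specific estimates make that visible.
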